## Abstract

**Background:**

Since the start of the COVID-19 pandemic, efforts have been made to develop early warning risk scores to help clinicians decide which patient is likely to deteriorate and require hospitalization. The RECAP (Remote COVID-19 Assessment in Primary Care) study investigates the predictive risk of hospitalization, deterioration, and death of patients with confirmed COVID-19, based on a set of parameters chosen through a Delphi process performed by clinicians. We aim to use rich data collected remotely through the use of electronic data templates integrated in the electronic health systems of several general practices across the United Kingdom to construct accurate predictive models. The models will be based on preexisting conditions and monitoring data of a patient’s clinical parameters (eg, blood oxygen saturation) to make reliable predictions as to the patient’s risk of hospital admission, deterioration, and death.

**Objective:**

This statistical analysis plan outlines the statistical methods to build the prediction model to be used in the prioritization of patients in the primary care setting. The statistical analysis plan for the RECAP study includes the development and validation of the RECAP-V1 prediction model as a primary outcome. This prediction model will be adapted as a three-category risk score split into red (high risk), amber (medium risk), and green (low risk) for any patient with suspected COVID-19. The model will predict the risk of deterioration and hospitalization.

**Methods:**

After the data have been collected, we will assess the degree of missingness and use a combination of traditional data imputation using multiple imputation by chained equations, as well as more novel machine-learning approaches to impute the missing data for the final analysis. For predictive model development, we will use multiple logistic regression analyses to construct the model. We aim to recruit a minimum of 1317 patients for model development and validation. We will then externally validate the model on an independent dataset of 1400 patients. The model will also be applied for multiple different datasets to assess both its performance in different patient groups and its applicability for different methods of data collection.

**Results:**

As of May 10, 2021, we have recruited 3732 patients. A further 2088 patients have been recruited through the National Health Service Clinical Assessment Service, and approximately 5000 patients have been recruited through the DoctalyHealth platform.

**Conclusions:**

The methodology for the development of the RECAP-V1 prediction model as well as the risk score will provide clinicians with a statistically robust tool to help prioritize COVID-19 patients.

**Trial Registration:**

ClinicalTrials.gov NCT04435041; https://clinicaltrials.gov/ct2/show/NCT04435041

**International Registered Report Identifier (IRRID):**

DERR1-10.2196/30083

## Introduction

### Trial Background and Rationale

Since the start of the pandemic, there has been extensive work [1-3] to develop risk scores for the management of patients with acute COVID-19 that can help to predict the risk of hospitalization, deterioration, and death.

There is pressure on clinical services, and evidence that a small percentage of patients experience precipitous deterioration (usually on about day 7 after symptom onset) [4]. For this reason, there is a growing clinical need to develop and validate an early warning risk tool to be used in a primary care setting that is specific to COVID-19 and based on data that can be reliably collected during a remote consultation.

The RECAP (Remote COVID-19 Assessment in Primary Care) trial (NCT04435041) was designed to develop an early warning tool for patients diagnosed with COVID-19 in primary care settings. The original study protocol [5] outlines the study rationale and data collection process. This paper describes the process for quantitative development and validation of the RECAP-V1 model. The primary objective is to produce a multivariable risk prediction tool to facilitate primary care physicians and other clinicians working in the community in the early identification of COVID-19 patients that are at higher risk of requiring hospital admission, and to inform the early escalation of their treatment, with the aim to expedite admission where necessary and decrease deaths.

To minimize the risk of data selection bias and data-driven interpretation of results, we here outline a prespecified statistical analysis plan (Version 1.0), which details all of the analysis steps to develop and validate the risk prediction model.

### Research Questions

We aim to answer the following research questions: (1) What is the optimum risk model for RECAP-V1 to predict hospital admission? (2) What are the sensitivity, specificity, and positive and negative predictive values of the RECAP-V1 risk tool as used in the primary care assessment of COVID-19 patients?

### Study Objectives

The primary objective of the study is the development of a data-driven risk tool (RECAP-V1) for use in general practitioner (GP)-patient consultations (mainly by phone or video) in the context of COVID-19. As a secondary objective, the early warning risk tool will be externally validated on an independent dataset. As a third objective, the performance of the model in additional datasets will be assessed. Data for both model development and model validation will be prospectively collected.

## Methods

### Design

RECAP is a prospective cohort observational study. Data are remotely collected through a questionnaire form outlined in the original study protocol [5] for study-specific data, with additional demographic data being collected through routine electronic health record systems run by participating clinical practices.

### Sample Size

#### Model Development and Internal Validation

Assuming that 10% of patients diagnosed with COVID-19 will be admitted to hospital [6], a 0.05 acceptable difference in apparent and adjusted Cox-Snell R-squared, 0.05 margin of error in estimation of the intercept, a binary outcome based on admission to hospital, and a maximum of 24 predictor parameters [5], we estimate that the minimum sample size required for new model development is 1317 participants enrolled for the development set [7].

#### External Validation

For assessment of the prediction accuracy of the model, the sample size was calculated based on the assumption that 85% specificity would be the lowest level worth carrying forward because lower values would be considered too low for such a model to be used to make clinical decisions. We focus on specificity, because we are keen for the model to correctly identify the true negatives (and reduce the number of false negatives) considering the risk associated with missing a diagnosis. Based on a 95% CI and precision of 0.05, we aim to recruit at least 1400 patients for model external validation, assuming 87% specificity and a hospitalization rate of 10%.

Assuming a loss to follow-up of 5%-6%, due to possible linkage failure or not recording admission, we aim to recruit at least 2880 participants.

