For each patient in this set, the result of the RECAP-V1 model will be calculated, and an ROC curve will be plotted from the highest to lowest values to determine the cut-off points for the predicted risk that optimize the specificity and sensitivity of the predictor model for red, amber, and green risk groups. The risk groups represent the relative risk of a particular patient outcome, with green signifying a very low risk, amber being a moderate to high risk, and red being a very high risk. This stratification ensures that there is a minimal number of false negatives in the final model and patients are not considered to be at low risk unless absolutely certain. The rate of increase and the point of inflection for the ROC curve will be used to inform the two cut-off points at the green/amber and amber/red points, which will be used as thresholds. The choice of optimum cut-off points is a clinical decision based on the shape of the resulting ROC curve (eg, how well-behaved the curve is, whether it is asymmetrical). Cut-off points should be clinically informative (ie, have a gradient representing the interval LR that is either greater than 2 or less than 0.5 so that the score changes the prior probability sufficiently). With a two cut-off point score for the red/amber/green (admit/monitor/advise) categories, the red/amber cut-off point should be in the steepest part of the curve (the most abnormal scores) where the LR will increase the risk of admission, and the amber/green cut-off point should be in the shallow part of the curve (the least abnormal scores) where the LR will decrease risk of admission. The ROC curve will thus be divided into three parts from the most abnormal to the least abnormal with three associated interval LRs; we will aim to allocate scores based on maximizing the “most abnormal” interval LR and minimizing the “least abnormal” interval LR with the middle interval LR likely to be around 1. There are several statistical tools for finding these points; however, in our opinion, selecting appropriate points from inspection of the ROC has the highest clinical validity [15].

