#### Objective 2: External Validation of the Model

The model accuracy will then be assessed externally using the RSC Practice network data to verify the specificity of the model predictions, as well as the sensitivity, negative predictive value, and positive predictive value [16,17].

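### External validation is built on specificity in order to limit false negatives, but specificity does not measure them, and no target or precision is set for sensitivity

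*SAP article*

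**What the plan says.** All references are to the SAP article.

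- **Sample Size, External Validation.** The size rests on the assumption that "85% specificity would be the lowest level worth carrying forward". The reason given is "We focus on specificity, because we are keen for the model to correctly identify the true negatives (and reduce the number of false negatives"), and the sentence ends "considering the risk associated with missing a diagnosis". The calculation follows: "Based on a 95% CI and precision of 0.05, we aim to recruit at least 1400 patients for model external validation", with an expected specificity of 87% and 10% of patients hospitalized.
- **Model Internal Validation and Evaluation.** Two cut-offs divide predicted risk into red, amber and green, with the aim again expressed through false negatives: "This stratification ensures that there is a minimal number of false negatives in the final model". Cut-offs are chosen by inspecting the ROC curve. They should give an interval likelihood ratio (LR) above 2 or below 0.5, with the LR of the least abnormal band made as small as possible.
- **Objective 2.** The RSC network data are used "to verify the specificity of the model predictions". Sensitivity and both predictive values are reported as well, without a target for any of them.
- **Research Questions.** The second question asks for all four accuracy measures.

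No expected value, minimum or precision for sensitivity appears anywhere in the article.

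**The concern.** Specificity is TN/(TN+FP), calculated among patients who are not admitted. A false negative is an admitted patient placed below the cut-off, and the rate of such errors is FN/(TP+FN) = 1 − sensitivity. The reason given for the choice therefore supports a different measure from the one chosen. On a given ROC curve the two also pull against each other: a cut-off moved to raise specificity lowers sensitivity and adds false negatives.

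The article says that it fixes the analysis in advance to limit data-driven interpretation. For the error it describes as the important one, it leaves the reader of the validation results with no prespecified standard. The one figure presented as a minimum does not address that error. Nor is it attached to a cut-off, although a three-band score has two specificities.

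**Working it through.** **Inputs from the article:** specificity minimum 0.85, expected specificity 0.87, 95% CI, precision 0.05 (read as the half-width), 10% admitted, N = 1400, LR guidance above 2 or below 0.5. **Assumed here:** sensitivities of 0.85 to 0.90, since the article gives none.

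**1. The plan's own figure.** For a half-width d on specificity, N = 1.96² × p(1 − p) / d² / (1 − prevalence).

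- Stated inputs: 3.8415 × 0.87 × 0.13 / 0.0025 / 0.90 ≈ 194. The stated 1400 is not reproduced.
- With 0.05 read as the full width (d = 0.025): 773.
- With d = 0.02, the distance from 87% to 85%: 1207.
- For comparison, a sensitivity of 0.90 with d = 0.05, dividing by the 10% admitted: 3.8415 × 0.90 × 0.10 / 0.0025 / 0.10 ≈ 1383. This is close to 1400, but the article states no such input.

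The 1400 is a number after losses: (1317 + 1400)/0.95 = 2860 and (1317 + 1400)/0.94 ≈ 2891, which bracket the stated total of 2880. So 140 admitted and 1260 not admitted are the right bases below.

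**2. Precision that 1400 patients deliver.** Half-width = 1.96 × √(p(1 − p)/n).

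| Measure | p | n | Half-width |
|---|---|---|---|
| Specificity | 0.87 | 1260 | 0.019 |
| Sensitivity | 0.90 | 140 | 0.050 |
| Sensitivity | 0.87 | 140 | 0.056 |
| Sensitivity | 0.85 | 140 | 0.059 |

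Specificity is estimated far more precisely than the stated 0.05. Sensitivity is close to 0.05 or slightly worse.

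**3. How far the LR guidance limits false negatives.** Take the 85% to apply at amber/green. The LR of the green band is (1 − sensitivity)/specificity.

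- LR < 0.5 at specificity 0.85: 1 − sensitivity < 0.5 × 0.85 = 0.425, so sensitivity > 0.575. Up to about 43% of admitted patients could be green, just under 60 of 140.
- At specificity 0.87: 1 − sensitivity < 0.435, so sensitivity > 0.565.
- The negative predictive value at the first limit is 0.9 × 0.85 / (0.9 × 0.85 + 0.1 × 0.425) = 0.765/0.8075 ≈ 0.947, against 0.900 with no tool at all. Without a target, that figure would look reassuring.

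Now take the 85% to apply at red/amber. The LR of the red band is sensitivity/(1 − specificity), and LR > 2 needs only sensitivity > 2 × 0.15 = 0.30. Patients below that cut-off include the amber band, which the article labels for monitoring, so they cannot all be counted as missed. On this reading the 85% says nothing about the green band.

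**The case against.** The best defence is that the 85% is a planning assumption and that the plan looks at more than specificity. Much of this stands. Objective 2 contains no formal pass/fail rule, all four measures are to be reported, and a low sensitivity would be visible. The cut-offs are placed by LR and ROC inspection in the development data, not by the 85%, and the plan aims to make the green-band LR as small as possible. The real figure may therefore be well below 43%.

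Three stronger readings are tempting, and the documents do not support them.

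- *A rule that labels everyone green would pass.* Its LR is 1, which the cut-off guidance excludes.
- *The plan accepts a model that misses about half of admitted patients.* Under an assumed equal-variance binormal ROC at 87% specificity, AUC 0.75 and 0.80 give sensitivities of 0.43 and 0.53. At amber/green the LRs would be 0.568/0.87 = 0.65 and 0.475/0.87 = 0.55, both outside the guidance. At red/amber the count would include monitored amber patients. The article gives no AUC either; at an assumed 0.90 and specificity 0.85 to 0.87, about 22 to 25% fall below the cut-off.
- *The 1400 was really derived from sensitivity.* It lies near 1383, but the text says specificity, and nothing in it shows another origin.

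What the defence does not answer is that the LR guidance applies to cut-off selection in the iCare data and is not a criterion for the external validation. Reporting sensitivity without a target is also not a prespecified standard.

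**Conclusion.** The concern holds in a limited form. The rationale in External Validation is wrong: specificity cannot show whether false negatives are few. Sensitivity has no expected value, minimum or precision, and the specificity minimum is not tied to a cut-off. With the LR guidance respected at amber/green and specificity at 85%, up to about 43% of admitted patients could still be classed green. That is an upper limit under this reading of the cut-off, not a prediction of how the model will perform. Separately, the stated inputs give about 194 patients and do not support 1400.

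This should be fixed. It does not invalidate the design, because the needed measures are already planned and 1400 patients give usable precision for sensitivity. The precision figures rest on the article's 10% admission rate and on assumed sensitivities.

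**What to change.** 1. In External Validation, correct the sentence so that false negatives are linked to sensitivity.
2. Name the cut-off (green/amber or amber/red) to which the 85% and 87% specificity apply.
3. Before the validation data are analysed, add to Objective 2 a minimum for sensitivity, or for an equivalent false-negative measure, at the green/amber cut-off. It stands alongside the specificity minimum, and its value is for the investigators to choose.
4. State the precision that 1400 patients with 140 admitted deliver: about ±0.050, ±0.056 and ±0.059 at sensitivity 0.90, 0.87 and 0.85, and about ±0.019 for specificity at 0.87.
5. Correct the derivation of 1400, or give the inputs that produce it.

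The cost is wording and a few restated figures, with no extra patients. The downside is that the stated sensitivity precision is slightly worse than 0.05 at 0.85 to 0.87. Holding ±0.05 there would need 1960 or 1738 patients, which is an option and not a requirement.

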## Results

A total of 173 active primary care practices have enrolled for the recruitment of patients across the iCare and RSC practice network. As of May 10, 2021, the study has recruited a combined sample of 3732 participants for the development, validation, and accuracy assessment of the model. A total of 2429 participants have been recruited from North West London GP practices (iCare), including the primary care data on the patients’ signs and symptoms during the full 28-day follow-up period; 1303 patients have been recruited from RSC practices, similarly recording the signs and symptoms of patients over the full 28-day follow-up period.

Through the DoctalyHealth platform, data have been collected using a remote monitoring system to record the patients’ clinical parameters, as well as signs and symptoms. The dataset comprises approximately 5000 patients and will be used to develop a model for this patient set. Additionally, 2088 patients have been recruited through NHS111 CCAS.

The final results of the model development and validation will be reported following the TRIPOD guideline [28] for prediction model development and validation. This study is expected to conclude in December 2021.

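### The 1400 patients for external validation do not follow from the stated inputs, which give about 194; the achieved precision and the use of the 85% floor need restating

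*SAP article*

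**What the plan says.** Under Sample Size, External Validation, the SAP article starts from a floor: "85% specificity would be the lowest level worth carrying forward". It then gives the derivation: "Based on a 95% CI and precision of 0.05, we aim to recruit at least 1400 patients for model external validation", with an expected specificity of 87% and a hospitalization rate of 10%. The abstract repeats the size: "We will then externally validate the model on an independent dataset of 1400 patients".

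The same section closes with one recruitment total after 5%-6% loss to follow-up: "we aim to recruit at least 2880 participants". The development minimum, in the preceding subsection, is 1317. Definition of Analysis Population assigns iCare to development and the RSC Practice network to external validation. Results reports 3732 recruited by 10 May 2021, made up of 2429 from iCare and 1303 from RSC ("1303 patients have been recruited from RSC practices"), with the study expected to conclude in December 2021.

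**The concern.** The plan prints a complete set of inputs for a precision-based sample size and says that 1400 rests on them. A reader who puts those inputs into the usual formula does not get 1400, or anything near it. Either an input is misreported or the size came from another calculation, and the reader cannot tell which precision the validation was designed to deliver.

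The stated precision also sits badly with the stated purpose. The expected specificity is only 2 percentage points above the floor, while the half-width is 5 points. The plan does not say how the floor will be applied, so the reading of the validation result against 85% is left open.

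Finally, the loss allowance is attached to a pooled total, although the two datasets have separate roles and a surplus in one cannot make up a deficit in the other.

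**Working it through.** **Inputs** (all from Sample Size, External Validation, unless noted): z = 1.96 for a 95% CI; d = 0.05; expected specificity 0.87; hospitalization 10%, so 90% of patients inform specificity; floor 0.85; stated N = 1400; loss 5%-6%; development N = 1317 (Model Development and Internal Validation); RSC count 1303 (Results).

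**1. Attempt to reproduce 1400.** Formula: n = z² × Sp × (1 − Sp) / d², then divided by the fraction of patients who inform the estimate.
- Non-admitted patients: 1.96² × 0.87 × 0.13 / 0.05² = 173.8, so 174.
- All patients: 173.8 / 0.9 = 193.1, so 194. The ratio is 1400 / 194 = 7.2.
- 0.05 as full width (d = 0.025): 695.2 / 0.9 = 772.
- Divided by the admitted 10%, as for sensitivity: 173.8 / 0.1 = 1738.
- Continuity correction: 215. Clopper-Pearson: 214 (half-width) or 259 (lower arm).

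None of these reaches 1400. Values within 3% of it appear only when a stated input is changed: 0.85 with d = 0.02 over 0.9 gives 1361; 0.90 with d = 0.05 over 0.1 gives 1383; 0.85 with z = 1.645 over 0.1 gives 1380. The document supports none of these substitutions.

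**2. What 1400 delivers.** Non-admitted: 1400 × 0.9 = 1260. Half-width for specificity: 1.96 × √(0.1131 / 1260) = 0.0186. Admitted: 140. The plan gives no expected sensitivity; if 87% is assumed for illustration, the half-width is 1.96 × √(0.1131 / 140) = 0.056.

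**3. Against the 85% floor.** At the stated precision, 0.87 ± 0.05 is 0.82 to 0.92, which contains 0.85. At 1400 the expected lower limit is 0.87 − 0.0186 = 0.851, just above the floor. Exact binomial probability that the 95% lower limit exceeds 0.85, with 1260 non-admitted:

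| True specificity | Wilson limit | Wald limit |
|---|---|---|
| 0.87 | 0.527 | 0.561 |
| 0.88 | 0.875 | 0.891 |

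**4. Pooled target.** 1317 + 1400 = 2717, and 2717 × 1.06 = 2880, so this figure reproduces. Dividing by the retained fraction gives 2717 / 0.95 = 2860 and 2717 / 0.94 = 2891, which bracket it. By dataset:
- iCare: 1317 / 0.95 = 1387 to 1317 / 0.94 = 1402.
- RSC: 1400 / 0.95 = 1474 to 1400 / 0.94 = 1490.

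**5. RSC at the reported date.** 1303 is 97 below 1400 before loss. After loss, 1303 × 0.94 = 1225 to 1303 × 0.95 = 1238. With 1225 evaluable (about 1102 non-admitted), the specificity half-width is 1.96 × √(0.1131 / 1102) = 0.020. With about 122 admissions, the sensitivity half-width is about 0.060 on the same assumed 87%.

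**The case against.** The strongest reply is that nothing is lost. The plan recruits far more than its stated precision needs, so ±0.05 for specificity is met with a wide margin, and no estimate or analysis changes. That stands, and it limits the point to a mismatch between the stated size and the stated precision. A reader might infer that the validation is undersized for its stated aim; the figures show the opposite for specificity.

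A reader might also infer that the design fails its own criterion. The documents do not support this. They call 85% the lowest level worth carrying forward, but they set no test, no power and no rule that the lower confidence limit must exceed it. If the floor applies to the point estimate, the 53-56% is not the relevant figure. What remains is that the plan names the floor as the basis of the calculation, states a precision too wide to distinguish 87% from it, and leaves its application undefined.

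A third tempting reading is that the pooled 2880 conceals a shortfall in the validation set. That is too strong. The plan states 1400 separately for validation, and Results gives the RSC count beside the combined one; only the abstract's Results pools the two. The 1303 is an interim count, and the document does not say that RSC recruitment had closed. The effect on precision is also small: ±0.019 becomes ±0.020 for specificity. What stands is narrower: an allowance applied only to the total does not protect the RSC set.

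**Conclusion.** The point holds as a reporting and arithmetic error. The printed inputs give about 194 patients, not 1400, and no reading that keeps those inputs gives 1400. This rests on the standard normal-approximation formula with 0.05 as the half-width; the full-width, continuity-corrected and exact versions do not change the conclusion.

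The actual design is more precise for specificity than stated, by a factor of about 2.7 in half-width (0.05 / 0.0186). Its ability to separate 87% from 85% is nevertheless close to even odds if the floor is meant for the lower limit. The figure for sensitivity depends on an assumed 87% that the plan does not give. Whether RSC finally fell short of 1400 cannot be known from this document.

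**What to change.** In Sample Size, External Validation:

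1. Give the formula and inputs that actually produce 1400. Failing that, keep 1400 and restate the precision: about ±0.019 for specificity at 0.87 (1260 non-admitted) and, labelled as an assumption of 87% sensitivity, about ±0.056 for sensitivity (140 admissions).
2. State whether the 85% floor applies to the point estimate or to the lower 95% limit. If the lower limit, report the chance of clearing it with 1400: about 53-56% at a true 0.87 and about 87-89% at a true 0.88.
3. Replace the single 2880 with loss-adjusted targets by dataset: about 1387-1402 for iCare and 1474-1490 for RSC.
4. If RSC closes below its target, report the precision at the number achieved. At about 1225 evaluable patients this is about ±0.020 for specificity.

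The cost is SAP wording and restated figures, settled before the validation analysis. No added enrolment is needed.
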